### Outcome measures

The primary outcome is daily total active time (minutes per day), defined as time spent in non-lying postures (sitting on bed edge, sitting in chair, standing, walking, exercising) as continuously measured by the PreSAGE system. This outcome is aggregated daily and analysed as a within-patient time series. The validity of this AI-derived measure will be established against clinician-rated ground truth during Phase 2 validation (accuracy, precision, recall, F1, and AUROC), and only activity states meeting a pre-specified per-class reliability threshold (F1 ≥ 0.80) will contribute to the primary metric; states with lower reliability (for example, small-motion exercises) are reported descriptively and excluded from the primary outcome. Because individual rehabilitation prescriptions are heterogeneous and patient-specific, personalised therapist-set goals are evaluated as a patient-referenced secondary outcome rather than folded into the primary measure, which is defined identically for all participants to preserve comparability across the cohort.

Secondary quantitative outcomes include: (a) daily number and duration of sitting-out-of-bed episodes; (b) daily exercise frequency and duration, disaggregated by upper and lower limb exercises; (c) daily proportion of prescribed exercises completed (exercise compliance rate); (d) number of goals set and achieved per day; (e) dashboard utilization (daily interaction count and duration); (f) FIM score change from admission to discharge; (g) FAC score change; (h) MBI score change; (i) length of stay (days); (j) discharge destination (home, community hospital, skilled nursing facility); (k) incidence of complications (pressure injuries, deep vein thrombosis, falls, hospital-acquired infections); (l) nursing engagement frequency and duration across activity types (wound dressing, diaper change, dressing, intravenous management, patient calls, nasogastric tube feeding, assisted feeding, medication administration, vital signs monitoring), recorded as episode count and cumulative minutes per day; (m) time to first sit-out-of-bed episode post-admission; (n) complication rates (pressure injuries, deep vein thrombosis) analyzed by functional level subgroup.

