Additionally, Monte Carlo power simulations (2,000 replications) were conducted to evaluate the study's ability to detect intervention effects under the piecewise multilevel growth model. Data were generated assuming 50 participants (10 per onset stratum), a median of 24 daily observations each (based on Phase 1 empirical length of stay; IQR 15–35 days), a within-person residual standard deviation of 25 min, between-patient intercept standard deviation of 40 min, and within-person autocorrelation of 0.3. The study has greater than 80% power to detect an immediate level change of 10% in daily active time at dashboard onset (18 min; *α* = 0.05, two-sided), and greater than 99% power for a 15% level change (27 min, within-person d = 1.08). The study is primarily powered for the immediate level change parameter (*γ*₂₀); detection of the sustained slope change parameter (*γ*₃₀) would require larger per-day effects given the relatively short post-onset observation period. The sample of 50 provides adequate headroom for anticipated data attrition (early discharge, camera downtime) and planned subgroup analyses by functional level. We note that, while the sample is adequately powered for the primary immediate level-change parameter, the planned functional-level subgroup comparisons and the sustained slope-change parameter are powered to detect only larger effects given the shorter post-onset observation window; these analyses are therefore pre-specified as exploratory and hypothesis-generating rather than confirmatory.

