### Randomization and blinding

Randomization of dashboard onset timing will be performed using a computer-generated random number sequence, consistent with recommendations for randomized SCEDs (27, 28). Allocation will be concealed using sequentially numbered, opaque, sealed envelopes prepared by a statistician not involved in recruitment. Patients will be stratified by primary diagnosis (stroke vs. non-stroke) and baseline functional level [dependent [FIM motor score ≤58] vs. independent [FIM motor score >58]] to ensure balanced representation across onset strata. Neither patients nor clinical staff can be blinded to dashboard activation, as the intervention involves an active visual feedback display. However, the primary outcome (daily active time) is measured objectively and continuously by the PreSAGE system, eliminating observer bias in outcome ascertainment. The statistician conducting the primary analysis will be blinded to onset stratum assignments.

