Secondary analyses for clinical outcomes (FIM, FAC, MBI, length of stay, discharge destination, complications) will use generalized linear models adjusted for baseline characteristics. Dashboard utilization patterns will be explored using descriptive statistics and latent class analysis to identify distinct engagement profiles. Subgroup analyses will compare intervention effects between functionally dependent and independent patients, with the hypothesis that dependent patients may show primary improvements in clinician-mediated outcomes (nursing engagement frequency, time to first sit-out, complication rates) while independent patients may show primary improvements in self-directed activity outcomes (daily active time, exercise compliance, dashboard utilization). The dose-response relationship between dashboard interaction frequency and activity changes will be examined using the interaction count as a time-varying covariate in the multilevel model.

All quantitative analyses will be conducted using R (R Foundation for Statistical Computing, Vienna, Austria) with the “lme4”, “nlme”, 'SingleCaseES', and “brms” packages.

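### The complication outcome analysed by functional level leaves out falls and hospital-acquired infections, so a benefit claimed in dependent patients could be reported without the matching falls result.

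*Protocol article*

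**What the plan says.** All references are to the protocol article.

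Under Outcome measures, complications appear as two separately lettered secondary outcomes. The first has no subgroup: "k) incidence of complications (pressure injuries, deep vein thrombosis, falls, hospital-acquired infections". The second is the subgroup version: "n) complication rates (pressure injuries, deep vein thrombosis) analyzed by functional level subgroup". The text does not explain why the second list is shorter.

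The Quantitative analysis section uses complications in two places. The general analysis sentence reads "Secondary analyses for clinical outcomes (FIM, FAC, MBI, length of stay, discharge destination, complications) will use generalized linear models adjusted for baseline characteristics" and does not itemise the word. The subgroup plan reads "Subgroup analyses will compare intervention effects between functionally dependent and independent patients". Its expectation for the first of these two groups includes a complication benefit: "dependent patients may show primary improvements in clinician-mediated outcomes (nursing engagement frequency, time to first sit-out, complication rates". The components are again not itemised.

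Functional level is defined under Randomization and blinding: "baseline functional level [dependent [FIM motor score ≤58] vs. independent [FIM motor score >58". Of the functional-level comparisons and the slope-change parameter, the Sample size justification says that "these analyses are therefore pre-specified as exploratory and hypothesis-generating rather than confirmatory".

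**The concern.** The intervention aims to increase time in non-lying postures. According to The DREAMT intervention section, the care team of a dependent patient uses the activity data to guide turning and early mobilisation. Pressure injury and deep vein thrombosis are events that such changes could plausibly reduce. Falls are the event in (k) that more sitting out, standing and transferring could plausibly increase. The document itself treats leaving bed as something to watch: the Introduction says the existing system is deployed for bed-exit prevention, and the Results section describes a dashboard toggle separating assisted from unassisted bed exits for nursing risk assessment.

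The subgroup list therefore keeps two events on which a benefit is plausible and omits the one on which harm is plausible, in the subgroup where a complication benefit is hypothesised. The result will also be used: the Mixed-Methods integration section draws on the subgroup analyses to answer for whom, and under what conditions, the intervention works. At stake is the balance of that statement for dependent patients. The primary outcome, the sample size and the primary analysis are not affected.

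**Working it through.** The plan gives no figure to reproduce and no complication rate to calculate with, so the check is a comparison of the text.

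**Step 1. The two component lists (Outcome measures).**

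| Event type | Outcome (k), no subgroup | Outcome (n), by functional level |
|---|---|---|
| Pressure injuries | yes | yes |
| Deep vein thrombosis | yes | yes |
| Falls | yes | no |
| Hospital-acquired infections | yes | no |
| Number of components | 4 | 2 |

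The difference is 4 − 2 = 2 components: falls and hospital-acquired infections.

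**Step 2. Which list the subgroup hypothesis uses.** The hypothesis for dependent patients names three outcomes in this order: nursing engagement frequency, time to first sit-out, complication rates. Under Outcome measures, nursing engagement is (l), time to first sitting out of bed is (m), and complication rates are (n). The order matches. The noun also matches: (n) speaks of rates, while (k) speaks of incidence and the general model sentence says only complications. The likeliest reading is that the hypothesis rests on (n), the two-item list. This is an inference, because the text does not say so.

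**Step 3. Where falls are still reported.** Falls remain a component of (k), and complications are to be analysed with generalized linear models adjusted for baseline characteristics. The Ethical considerations section adds a safety monitoring plan in which adverse events are independently reviewed each quarter. Neither provision commits to showing falls separately for dependent and independent patients. The sentence on subgroup analyses is general enough to permit such a breakdown but does not require it. The only complication outcome listed by functional level is (n).

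**Step 4. What follows.** If the plan is followed as listed, the complication result in dependent patients consists of pressure injury and deep vein thrombosis, with no pre-listed falls figure for the same patients. The size of any resulting distortion cannot be derived. The document gives neither event rates nor the expected split of the 50 patients at the FIM motor cut-off of 58.

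**The case against.** The strongest reply is that nothing here conflicts. Outcomes (k) and (n) have separate letters, each itemises its own components, and both can be computed without ambiguity. Outcome (n) may be a deliberate subset: pressure injury and deep vein thrombosis are the events that turning and mobilisation would be expected to influence, and restricting a subgroup hypothesis to what the mechanism targets is defensible. Falls are kept for every patient under (k), adverse events are reviewed quarterly, and the subgroup comparison is declared exploratory.

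Most of this stands. It means that the point is not a contradiction and that falls data are not missing from the study. It leaves two gaps: the restriction is not explained, and no provision puts falls beside the two-item rate in the subgroup where a benefit is hypothesised. Exploratory status lowers the weight of the result but does not balance what is shown.

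A reader might go further and infer that one endpoint has two conflicting definitions, that the list was chosen to favour the intervention, or that the main harm is hidden in the group most exposed to it. The document does not support these readings. It gives no motive for the list, does not call falls the main harm, and does not say that dependent patients are most exposed to them. Nor can one claim that the conclusion would change sign between the lists. Hypothetical counts can be picked to make that happen, but without event rates they are no evidence that it will.

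A further objection concerns the remedy: pooling all four events into one subgroup rate would let opposite effects cancel. That is correct and shapes the fix.

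**Conclusion.** The point holds as a reporting gap in a secondary, exploratory analysis. The complication outcome listed by functional level omits two of the four event types counted in (k), without a stated reason. The hypothesis of better complication rates in dependent patients appears to rest on that shorter list. A favourable result on immobility-related events could therefore be reported in that subgroup without the matching falls result, although falls are captured overall.

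This rests on two assumptions: that complication rates in the hypothesis means outcome (n), as the wording and order suggest, and that more time out of bed could plausibly raise falls, which is a clinical premise that the document does not quantify. No direction or size of effect can be stated. The change is worth making because it is cheap and makes the subgroup conclusion balanced, not because the main result is in doubt.

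**What to change.** - Extend outcome (n) so that all four components of (k) are reported by functional level, each on its own line. Always show falls beside pressure injury and deep vein thrombosis, not only within a pooled rate.
- In the Quantitative analysis section, name the components that the hypothesis on complication rates in dependent patients covers. If it is meant to stay with pressure injury and deep vein thrombosis, say so and give the reason in one sentence; the four-line report still accompanies it.

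Falls and hospital-acquired infections are already outcomes under (k), and functional level is already recorded for stratification, so no new data are needed. The cost is a small wording change and a few extra descriptive rows. With 50 patients divided by functional level the counts will be sparse, so these rows should be presented as descriptive.

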### Sample size justification

Sample size estimation for the RMBD follows guidance from Kratochwill et al. (27) and Shadish et al. (41) on single-case experimental designs adapted for group-level analysis. The key considerations are: (a) the number of data points per phase per participant, and (b) the number of participants (replications).

With a median length of stay of 24 days (mean 27.3, SD 17.0) based on Phase 1 data, and randomized onset at days 3–7, each patient will contribute 3–7 baseline data points and a variable number of intervention data points. At the median stay, intervention points range from 17 to 21 days. Approximately 18% of Phase 1 patients had stays under 14 days; these patients will be included in the intention-to-treat analysis but contribute fewer post-onset observations. Shadish et al. (41) recommend a minimum of 3–5 data points per phase for SCED analyses. For the group-level multilevel analysis, we follow Moeyaert et al. (42), who demonstrated that 30 or more participants provide adequate power (>80%) for detecting medium effect sizes (d = 0.5) in multilevel models of SCED data with 20 time points per participant. Our planned sample of 50 patients with 21 daily data points each substantially exceeds this threshold.

Additionally, Monte Carlo power simulations (2,000 replications) were conducted to evaluate the study's ability to detect intervention effects under the piecewise multilevel growth model. Data were generated assuming 50 participants (10 per onset stratum), a median of 24 daily observations each (based on Phase 1 empirical length of stay; IQR 15–35 days), a within-person residual standard deviation of 25 min, between-patient intercept standard deviation of 40 min, and within-person autocorrelation of 0.3. The study has greater than 80% power to detect an immediate level change of 10% in daily active time at dashboard onset (18 min; *α* = 0.05, two-sided), and greater than 99% power for a 15% level change (27 min, within-person d = 1.08). The study is primarily powered for the immediate level change parameter (*γ*₂₀); detection of the sustained slope change parameter (*γ*₃₀) would require larger per-day effects given the relatively short post-onset observation period. The sample of 50 provides adequate headroom for anticipated data attrition (early discharge, camera downtime) and planned subgroup analyses by functional level. We note that, while the sample is adequately powered for the primary immediate level-change parameter, the planned functional-level subgroup comparisons and the sustained slope-change parameter are powered to detect only larger effects given the shorter post-onset observation window; these analyses are therefore pre-specified as exploratory and hypothesis-generating rather than confirmatory.

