### Objectives

The primary objective is to evaluate the effectiveness of the DREAMT intervention (PreSAGE thermography-based AI monitoring with activity feedback dashboard) in increasing daily patient physical activity levels during inpatient rehabilitation, using a randomized multiple baseline design across participants.

The secondary objectives are to: (1) assess the impact on clinical rehabilitation outcomes, including Functional Independence Measure (FIM) scores, Functional Ambulation Category (FAC) scores, Modified Barthel Index (MBI), length of stay, discharge destination, and complications; (2) evaluate the effect on nursing workload distribution and time allocation; (3) explore the experiences, perceptions, and recommendations of patients, nursing staff, and therapists through semi-structured interviews; and (4) integrate quantitative and qualitative findings to develop a comprehensive understanding of intervention effectiveness and implementation considerations.

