### The DREAMT intervention

The DREAMT intervention is a multi-component digital health intervention comprising:
(1)*Continuous thermographic monitoring:* The PreSAGE system provides automated 24-hour activity data capture, processing, and classification using validated AI algorithms.(2)*Patient-facing feedback dashboard:* For functionally independent patients, the dashboard is accessible via a bedside tablet, displaying daily activity summaries (active time, sitting episodes, exercise counts), graphical progress toward personalized goals, and motivational prompts. For functionally dependent patients who may be unable to independently access the tablet, the dashboard functions primarily as a clinician-facing tool, with the care team using activity data to guide nursing engagement, turning schedules, and early mobilization decisions.(3)*Therapist-guided goal setting:* At the point of dashboard activation, therapists set initial personalized activity goals (e.g., daily minutes of sitting out of bed, exercise repetitions) based on the patient's baseline data and clinical status. Goals are reviewed and adjusted every 2–3 days using dashboard data.(4)*Clinician-facing dashboard:* Providing the care team with activity trend data, nursing engagement metrics, sleep indicators, and patient progress visualizations to support clinical decision-making and care coordination.

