### Data analysis

#### Quantitative analysis

The primary analysis will use a piecewise multilevel growth model (42, 45) to estimate the within-person effect of dashboard activation on daily active time. This analytic approach is well-established for combining data from multiple SCEDs into a unified multilevel framework (42). The two-level model (Level 1: daily observations nested within Level 2: patients) will take the form:
*Level 1: Y*ti* = β*0i* + β*1i*(Day*ti*) + β*2i*(Phase*ti*) + β*3i*(Day_post*ti*) + e*ti*Level 2: β*0i* = γ*00* + u*0i*; β*1i* = γ*10* + u*1i*; β*2i* = γ*20* + u*2i*; β*3i* = γ*30* + u*3iwhere Yti is the daily active time for patient *i* on day *t*; Dayti is the centered day variable; Phaseti is a binary indicator (0 = baseline, 1 = post-dashboard); Day_postti captures the post-activation trend (0 during baseline, days since activation during intervention); *β*2i captures the immediate level change (jump in activity at dashboard onset); *β*3i captures the change in slope (sustained trend change); and eti is the residual error modeled with an AR(1) structure to account for serial autocorrelation.

The Level 2 equations model between-patient variation in intercepts and slopes as random effects. Fixed effects (*γ*00, *γ*10, *γ*20, *γ*30) represent the average population-level baseline, pre-intervention trend, level change, and slope change. The primary hypothesis test is that *γ*20 (average immediate level change) and/or *γ*30 (average sustained slope change) differ significantly from zero.

Sensitivity analyses will include: (a) adjusting for patient-level covariates (age, diagnosis, baseline FIM, Clinical Frailty Scale score) in Level 2 equations; (b) testing different lag specifications (immediate vs. 1-day delayed effect); (c) modelling onset stratum as a fixed effect to test whether timing of activation moderates the intervention effect; (d) excluding patients with fewer than 14 days of total data (approximately 18% based on Phase 1 length of stay distribution); and (e) using Bayesian estimation as a robustness check. All analyses will follow the intention-to-treat principle based on assigned onset day.

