## Discussion

### Principal considerations

This protocol describes a rigorous mixed-methods approach to evaluating a novel thermography-based AI monitoring and feedback system in inpatient rehabilitation. The randomized multiple baseline design across participants represents a significant methodological advance over the pre-post and simple interrupted time series designs that predominate in digital health evaluations in rehabilitation settings.

The RMBD is well-suited to this study context for several reasons. First, the continuous within-patient time-series data generated by thermographic monitoring creates an unusually rich dataset that is best exploited by designs that model individual trajectories rather than group means at discrete timepoints. Second, the randomization of dashboard onset timing across participants provides a credible basis for causal inference: if activity increases systematically coincide with dashboard activation at five different randomly assigned timepoints, the effect is unlikely attributable to maturation, history, or regression to the mean (27, 28). Third, the design is ethical, as all patients receive the intervention during their admission; the only variation is the timing of onset. Fourth, the design does not require a separate no-treatment control group or multiple wards, making it feasible within a single-site context.

The piecewise multilevel growth model further strengthens the analysis by simultaneously modelling the natural recovery trajectory (pre-intervention slope), the immediate effect of dashboard activation (level change), and the sustained effect (post-intervention slope change), while accounting for between-patient heterogeneity and within-patient autocorrelation (42, 45). This provides more nuanced inference than a simple pre-post comparison.

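### The only adequately powered primary parameter is the jump at activation, which does not match an objective of higher activity during the stay and can miss a lasting gain that builds up over a week

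*Protocol article*

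**What the plan says.** Objectives (Protocol article): the primary aim is to evaluate effectiveness "in increasing daily patient physical activity levels during inpatient rehabilitation".

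Sample size justification: "The study is primarily powered for the immediate level change parameter", γ20. Power is given as above 80% for an 18-min (10%) level change at onset and above 99% for 27 min (15%), two-sided α 0.05. The same section says that the slope change γ30 would need larger effects, and classes it as exploratory.

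Quantitative analysis: the coefficient behind γ20 "captures the immediate level change (jump in activity at dashboard onset". Day_post "captures the post-activation trend (0 during baseline, days since activation during intervention". The primary hypothesis test is that γ20 and/or γ30 ("average sustained slope change) differ significantly from zero"). No direction is required. The only sensitivity analysis on effect timing is a 1-day delay.

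Principal considerations: the model is said to estimate "the sustained effect (post-intervention slope change".

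The DREAMT intervention: "Goals are reviewed and adjusted every 2–3 days using dashboard data".

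**The concern.** The objective concerns activity over the stay, whereas the powered parameter concerns one moment in it. Feedback with repeatedly revised goals could plausibly act gradually, and a new bedside display could plausibly produce a short novelty response. The planned model has one straight baseline trend, one jump and one straight change of trend, so it represents neither shape. Part of a gain that builds up over the first week goes into the common Day slope instead of γ20, while a short early gain falls mostly into γ20.

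The term labelled as the sustained effect does not fill this gap. A constant gain that lasts to discharge has γ30 = 0. No stated contrast evaluates the effect later in the stay or averages it over the stay. A one-week response could therefore be read as meeting the objective, and a lasting gain of the planned size could be missed.

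**Working it through.** **Inputs from the document.** 50 patients, 10 per onset day 3–7; median 24 daily observations (IQR 15–35); residual SD 25 min; intercept SD 40 min; autocorrelation 0.3; effects of 18 and 27 min; two-sided α 0.05.

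**Assumptions not in the document.** Stays are either all 24 days, or lognormal with median 24 and IQR about 15–35, clipped to 4–70. There is either a random intercept only, or also random slopes (SD 2–3 min/day) with a between-patient SD of the jump of 15–20 min, or a jump SD of about 35 min. Day_post is 0 on activation day.

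**Method.** For a true mean effect profile μ, the expected coefficients of the planned model are (ΣX′V⁻¹X)⁻¹ ΣX′V⁻¹μ, with covariance (ΣX′V⁻¹X)⁻¹. The probability of a significantly positive γ20 is Φ(γ20/SE − 1.96).

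**Step 1: the plan's own figures.** With varying stays and a random intercept only, the SE of γ20 is 3.84.
- 18 min: 18/3.84 − 1.96 = 2.73, power 99.7%.
- 27 min: 27/3.84 − 1.96 = 5.07, power above 99.9%.

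Both printed lower bounds hold. Power close to those bounds needs a jump SD of about 35 min, which gives SE 6.36 with 24-day stays: 18/6.36 − 1.96 = 0.87, power 81%; 27/6.36 − 1.96 = 2.29, power 99%.

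**Step 2: two other profiles of the same size.** With varying stays and a random intercept only:
- 18 min for 7 days, then zero: γ20 = 13.7; 13.7/3.84 − 1.96 = 1.61, 95%.
- Linear rise from 0 on activation day to a lasting 18 min over 7 days: γ20 = 7.5; 7.5/3.84 − 1.96 = −0.01, 50%.

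Monte Carlo with estimated variances gave 94% and 47–50%. Across settings:

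| Setting | 7-day gain, then zero | Lasting, built up over 7 days |
|---|---|---|
| Varying stays, random intercept | 94–95% | 50% |
| Varying stays, random slopes, jump SD 15–20 | 92–95% | 17–22% |
| 24-day stays, the same settings | 96–100% | 14–19% |
| Jump SD 35 min | 59–81% | 10–21% |

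**Step 3: sensitivity to shape and coding.**
- Lasting gain complete by the third day (6, 12, 18 min): 45–92%. On the printed inputs with varying stays and a random intercept it is 92%, against 94% for the transient.
- Transient that fades linearly over the week: 39–94%.
- Seven-day rise already at 18/7 min on activation day: 69% (varying stays, random intercept).
- Day_post counted from 1 (varying stays, random intercept): 99% for the transient against 70–87% for the build-up.

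**Step 4: what γ30 adds.** Its SE is about 1.0–1.25 min/day. Its expected value is 0 for a constant lasting step, −0.3 to +0.6 for the build-up and −1.4 to 0 for the transient. Even −1.4 is little more than one SE from zero. γ30 is significantly positive for the build-up in only 1–8% of trials.

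Under the printed and/or rule, transient against 7-day build-up (the range covers starting at 0 or at 18/7 min):
- varying stays: 96% against 55–74%
- 24-day stays: 100% against 22–42%
- jump SD 33–35: 61–91% against 16–36%

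The slope test helps the transient slightly, because a significantly negative slope also counts.

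**Step 5: one week after activation.** Leave out the first 7 post-activation days and centre Day_post so that the Phase coefficient is the level at day 7. The estimates are then 18 min (build-up) and 0 (transient), with SE 10.9–12.6. The effect detectable with 80% power is 2.80 × 10.9 = 31 to 2.80 × 12.6 = 35 min. The baseline is 18/0.10 = 180 min, so this is 17–19%.

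**The case against.** The strongest reply is that the protocol is open about this. It calls the powered effect immediate, defines it as a jump, and says that the slope is weakly powered. That stands: no power figure is misstated. It does not settle the point, because the objective carries no such restriction and nothing links the claim to a later time.

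A second reply is that γ20 is what the stagger identifies best. Apart from weekend deferrals, no patient is still in baseline after day 7, so a later effect rests on extrapolating a short linear baseline. This also stands, and it explains the large day-7 SE. It is a reason to keep γ20, and equally a reason to limit what is concluded from it.

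A third reply is that the gap depends on chosen shapes. Initial goals are set at activation, so a quicker rise is plausible, and the gap may then nearly close. This is correct, and the sizes above are conditional on shape.

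A reader might infer that γ30 says nothing about persistence. That goes too far: with random slopes or equal 24-day stays its expected sign is negative for the transient and positive for the build-up. It is too imprecise to rely on, but not empty.

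A reader might also want the day-7 estimate to be significant before any claim about activity during the stay. A true, immediate, lasting 18-min gain would pass that test in only about 30–38% of trials (18/12.6 − 1.96 = −0.53; 18/10.9 − 1.96 = −0.31), so it should not be a gate.

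Finally, a statistical analysis plan that is not shown may contain later-time estimates. The parameter, the test and the power statement are nevertheless fixed in this article.

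**Conclusion.** The mismatch between objective and powered parameter is real. On the printed inputs and the assumptions listed, with Day_post starting at 0, an 18-min gain that stops after 7 days makes γ20 significant in about 92–100% of trials (59–81% with jump SD 35 min). A lasting 18-min gain built up linearly from zero over 7 days does so in about 10–50%. For that pair the ordering held in every setting run, under γ20 alone and under the and/or rule. The size depends on stay distribution, random-effect SDs, coding and above all effect shape.

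A reader might infer that the trial will announce a lasting benefit on the strength of a passing one, or that its stated power is false. The document supports neither: it nowhere says that a significant γ20 will be reported as lasting, and its power figures hold for the immediate effect they describe. What is missing is a statement of what those figures leave out and an estimate that speaks to later activity.

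Separately, the document contradicts itself on γ30, which is exploratory in the sample size section and part of the primary test in the analysis section.

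**What to change.** 1. In Sample size justification, keep the power figures. Add that they do not cover effects that build up after activation, and that about 31–35 min would be detectable with 80% power one week after activation, with the assumptions stated.
2. In Quantitative analysis, pre-specify a supportive estimate with 95% CI: the level one week after activation, from the same model with the first 7 post-activation days left out. It should not be a significance gate.
3. Word any conclusion from γ20 as an immediate change at activation. Report the later estimate and its imprecision beside any statement about activity during the stay.
4. Reconcile the exploratory status of γ30 with the and/or primary test, including the lack of a required direction, and stop labelling γ30 alone as the sustained effect.

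The cost is one extra fit, some wording, and a less favourable statement about lasting effects. Phase 3 is not expected before the end of 2026, so the change can be made before any evaluation data exist.
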